## Methods

### Study design and target population

In this intervention study, the population of the federal state of Thuringia, Germany, aged 60 years and above, forms the intervention group (*N* = 500,000). The intervention will take place in two consecutive influenza seasons (2017/18 and 2018/19, Fig. 1) and will be adapted in between. Changes in the outcomes will be compared to other German federal states and/or in a pre-post design depending on the outcome (specified below). Where possible, the analyses will follow a two-step analysis, first with an overall evaluation of the age group over 60 in general and then followed by analyses with special focus on the age group that will be identified as the main target group of the intervention.

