*Hypothesis.* In comparison with other federal states, the intervention region of Thuringia shows a greater reduction and respectively lower increase in incidence of influenza, pneumonia, IPD and sepsis.*Study population*. A retrospective database study is performed using state-wide hospital discharge data from patients over the age of 60 regardless of their vaccination status from 2014 to 2019 in the German Diagnosis Related Groups (DRG) statistics, which includes nearly complete inpatient billing data from all general hospitals in Germany. All data provided in the DRG statistics are anonymous. The DRG statistics is accessible by the Federal Statistical Office via controlled remote data processing legally based on the statistical data secrecy provision under section 16 of the Federal Statistics Act (Bundesstatistikgesetz). Each case contains a main diagnosis and up to 89 secondary diagnoses, hospital mortality and length of stay, procedures and patient demographics. We identify influenza, pneumonia, IPD and sepsis in patients aged ≥60 years in Thuringia (intervention group) and in the other 15 federal states of Germany by a list of ICD-10 GM codes. Cases with unknown age and gender will be excluded from analysis. As the data source for this study includes nearly complete inpatient data from nearly all acute-care hospitals in Germany (military or prison hospitals are excluded), it practically corresponds to a population-based survey, hence power calculations are not regarded as useful.*Outcome measures.* We identify hospital-treated influenza, pneumonia, IPD and sepsis cases and deaths in the period prior to and during the intervention in Thuringia (2014–2016, 2017–2019) and describe age- and sex-standardised incidence and mortality rates for the Thuringian population as of 31 December, 2014. To evaluate the intervention effect, we will compare incidence and mortality rates in Thuringia and the other federal states considering further confounding factors as vaccination behaviour.*Statistical analyses.* Trends of age- and sex-standardized incidence and mortality rates in the years 2014–2019 will be compared between the intervention group (population of the federal state Thuringia) and the control group (population from the other federal states). The data for analysis will be complete, except for the excluded cases with unknown age and gender (less than 0.002% expected); hence no particular missing data handling is necessary.

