*Retrospective nationwide study based on Multidisciplinary Quality Assurance in the Healthcare System (SQG) data of community-acquired pneumonia.*
*Hypothesis.* In comparison to the whole of Germany the intervention region of Thuringia shows a greater reduction and respectively lower increase in incidence rates and mortality rates of inpatients with community-acquired pneumonia.*Study population.* To assess the incidence rates of hospital-treated community-acquired pneumonia, retrospective data published by the Multidisciplinary Quality Assurance in the Healthcare System (SQG) will be used. As community-acquired pneumonia belongs to the services for the external inpatient quality assurance requiring documentation in Germany since 2005, data on age, sex, hospitalisation, severity of disease and in-hospital mortality rate among patients with community-acquired pneumonia will be obtained annually by the responsible quality department of SQG of Thuringia and all of Germany starting in 2014. All annual data published by SQG are anonymous and available with a delay of 7 to 8 months in the subsequent year. For a population-based study power calculations are not regarded as useful.*Outcome measures.* We identify incidence rates and in-hospital mortality rates of inpatients with community-acquired pneumonia for different age groups aged ≥60 years (60–69 years, 70–79 years, 80–89 years) and assess the severity of disease (distribution of CRB-65 score) [67] in the period prior to and during the intervention in Thuringia (2014–2016, 2017–2019) compared to all of Germany.*Statistical analyses.* Trends of age-specific annual incidence rates and in-hospital mortality rates of hospital-treated community-acquired pneumonia for age groups 60–69 years, 70–79 years and 80–89 years and mean changes of CRB-65 score will be compared between the intervention region Thuringia and all of Germany in the years 2014–2019. As SQG reports completeness of data in 100%, no missing data have to be considered. Currently, retrospective data published by SQG for hospital-treated community-acquired pneumonia are available for the years 2014, 2015 and 2016.
*Retrospective cohort study based on health insurance claims data.*

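### The SQG pneumonia study is labelled 60 and over but its trends stop at age 89, and its national comparator contains Thuringia (a minor dilution)

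*Protocol article*

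**What the plan says.** **Target group.** Under Study design and target population, "the population of the federal state of Thuringia, Germany, aged 60 years and above, forms the intervention group". No upper age limit is given there.

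**Age range in study c.** The outcome measures are incidence and in-hospital mortality of inpatients with community-acquired pneumonia "for different age groups aged ≥60 years (60–69 years, 70–79 years, 80–89 years". The statistical analyses list the bands again: "for age groups 60–69 years, 70–79 years and 80–89 years and mean changes of CRB-65 score". Neither place has a band for 90 and over or an open band from 80.

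**Comparator in study c.** The hypothesis reads "In comparison to the whole of Germany the intervention region of Thuringia shows a greater reduction", and the analysis says that trends "will be compared between the intervention region Thuringia and all of Germany in the years 2014–2019". Nothing says that Thuringia is taken out of the national figure.

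**Comparators elsewhere.** The Background announces a comparison with federal states that had no intervention. Study a (hospital discharge data) identifies cases aged 60 and over, with no upper limit, in Thuringia and "in the other 15 federal states of Germany". Study e (ASHIP claims data) sets Thuringia against the area outside it.

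**The concern.** Two features of study c do not fit the rest of the plan.

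1. The label and the list disagree. The label covers everyone from 60 upward; the list ends at 89. Because the same list appears in both the outcome measures and the analysis, a single slip is unlikely. Followed as written, the incidence and in-hospital mortality trends say nothing about the oldest part of the target group.
2. The control contains the treated region. Part of any change in Thuringia is therefore also counted in the comparator, which pulls the two series together and makes them dependent.

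At stake is how study c is read beside study a. The article wants its data sources to cross-validate one another, and for hospital-treated pneumonia these two studies are the natural pair. As planned they differ in age range and in comparator. If their results diverge, a reader could not at once tell a difference between data sources from a difference in definitions.

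**Working it through.** The article gives no sample size, power or event figure for study c, so there is no planned number to reproduce.

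**Step 1: age coverage.**
- Target group: 60 and over, open-ended (Study design and target population).
- Bands analysed: 60–69, 70–79, 80–89 (study c, given twice).
- Target minus bands: 90 and over. Coverage of this group in the two trends is nil.
- The trends are age-specific, so each listed band has its own numerator and denominator. Leaving out a further band does not change them: the loss is in coverage, not in the accuracy of the three rates.
- The CRB-65 comparison is named alongside the bands but is not explicitly confined to them, so the gap is established only for incidence and in-hospital mortality.
- The article gives no age distribution of pneumonia cases. If a fraction f of cases aged 60 and over are 90 or older, exactly f lies outside the trends. Taking f as 5–15% would be pure assumption; nothing in the article tests it.

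**Step 2: overlap of the comparator.** Let T be the rate in Thuringia, O the rate in the rest of Germany, G the national rate, and s Thuringia's share of the national denominator (population for incidence, pneumonia inpatients for in-hospital mortality).

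- G = s·T + (1 − s)·O
- T − G = T − s·T − (1 − s)·O = (1 − s)(T − O)

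The observed difference is therefore the difference from the rest of Germany multiplied by (1 − s). The same factor applies to a difference in changes over time if s is stable across 2014–2019.

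The article does not give s, so a range is assumed. For a difference T − O of −10:

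| assumed s | T − G | attenuation | factor to recover T − O, 1/(1 − s) |
|---|---|---|---|
| 1% | −9.90 | 1% | 1.0101 |
| 2% | −9.80 | 2% | 1.0204 |
| 3% | −9.70 | 3% | 1.0309 |
| 4% | −9.60 | 4% | 1.0417 |
| 6.25% (1/16, as if all 16 states were equal) | −9.375 | 6.25% | 1.0667 |

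The direction is fixed, toward no difference. The size is small throughout this range.

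**The case against.** **The source may impose both features.** Study c rests on annual figures that SQG publishes for Thuringia and for Germany, so the bands and the national total may simply be what is available. The article does not say so, but it cannot be ruled out. This stands as a limit on the remedy: a 90+ band may not be obtainable. It does not rescue a label of 60 and over on a list that ends at 89.

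**A reader might infer that the pneumonia results are biased by the age cut.** The documents do not support that. Rates are planned band by band, no pooled SQG rate for everyone over 60 is specified, and the three band rates are unaffected.

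**A reader might infer that studies a and c can no longer cross-validate each other.** That also goes too far. The discharge data are case-level with patient demographics, so their pneumonia rates can be tabulated for 60–69, 70–79 and 80–89. The Discussion already concedes in general terms that the sources may be hard to compare, although it names neither of these differences.

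**A reader might infer that the project loses the oldest patients or lacks a clean control.** It does not. Study a covers hospital-treated pneumonia from 60 upward against the other states, and study e includes community-acquired pneumonia codes with a comparator outside Thuringia. Study c is one of five secondary sources.

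**The overlap is openly stated and conservative.** This is correct. The national comparator is used consistently within study c, and the bias is toward the null. What remains is an avoidable departure from the comparators used in studies a and e.

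**Conclusion.** The point holds in a limited form. The age range is the main part: study c is labelled 60 and over, yet its incidence and in-hospital mortality trends omit everyone aged 90 and over, without a stated reason. That follows from the text alone. How many cases or deaths are involved cannot be determined from the article, and nothing in it shows that the share of deaths omitted exceeds the share of cases.

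The comparator is a minor second part. The attenuation equals Thuringia's share s exactly: 2–4% if s is assumed to be 2–4%, and 6.25% at the top of the range shown. For changes over time this also assumes a stable s. An overlap of this size would not by itself change the reading of study c.

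**What to change.** - **Age range.** Where the SQG data allow it, make the last band open (80 and over, or add 90 and over) in both the outcome measures and the statistical analyses. Where they do not, state the scope as 60–89 and give the reason.
- **Cross-validation.** If the scope stays at 60–89, tabulate the pneumonia rates from study a in the same three bands, beside its planned results for all ages from 60.
- **Comparator.** Where counts and denominators by band are available for both areas, subtract the Thuringian ones from the national ones, so that the control rate is (national cases − Thuringian cases) / (national denominator − Thuringian denominator). Where only rates and the share s are available, O = (G − s·T)/(1 − s) gives the same result. If neither is possible, keep the national comparator and report the attenuation with the value of s.

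The cost is a change of wording, one subtraction per band and year, and one extra table from study a. No new data collection is needed unless a 90+ band has to be requested from SQG, and the article does not show whether such a request could be met.

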##### Statistical analyses

Different methodological approaches will be considered to calculate vaccine uptake before and after the intervention. First, coverage will be calculated as the proportion of patients vaccinated per year (pneumococcus vaccination) or per season (influenza vaccination). The denominator will be taken from the KM6 statistics [65]. Second, vaccine uptake will be calculated among selected patients in a cohort approach [66]. Vaccine uptake will be calculated among those individuals who were < 60 years of age at the beginning of the observation period and turn 60 thereafter (thus have a new indication for the vaccine). For pneumococcus vaccination only, vaccine uptake will also be calculated for at-risk groups who have not been vaccinated in the last 5 years before the respective calendar year of interest and are thus recommended to receive the vaccine.

Vaccine uptake for both influenza and pneumococcus will be analysed by age, district, year/season/month and chronic underlying conditions (based on ICD-10 codes).

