*Hypothesis.* The incidences of influenza, pneumonia, IPD and sepsis are lower in people vaccinated than non-vaccinated over 60 years of age.*Study population.* To quantify the impact of influenza and pneumococcal vaccination on influenza, pneumonia, IPD and sepsis incidence and outcomes, a retrospective database study will be performed including about 300,000 persons ≥60 years, living in Thuringia, who are insured with one of the largest statutory health insurances in Germany (AOK PLUS, insured persons form about 40% of the Thuringian population). The exposed cohort group is expected to consist of about 130,000 patients with pneumococcal and/or influenza vaccination in 2014; the unexposed cohort group are patients without pneumococcal vaccination in 2008–2017 and without influenza vaccination in 2012–2017. The observation period covers the years from 2015 to 2017. The study is partly retrospective (2008–2016) and partly prospective (2017). The study was designed in 2017 and we have commenced in 2017 to acquire the data from 2008 to 2016 which are available from German SHIs with a regular delay of 9–12 months, so that the earliest time a SHI can transfer 2016 data is the end of 2017. Data preparation for statistical analysis has just begun and will not be finished before the end of 2018. As the inclusion of patients of 60 years and above in Thuringia insured with the SHI AOK PLUS practically corresponds to a complete survey, power calculations are not regarded as useful. All routine data collected by health insurances are anonymous.*Outcome measures.* Incidence rates and hospital/ICU admission rates of influenza, invasive pneumococcal diseases, pneumonia and sepsis, as well as in-hospital and long-term mortality will be compared between vaccinated and unvaccinated persons.*Statistical analyses.* Retrospective cohort study using adequate adjustment methods (multiple regression analysis, propensity score matching). The data for analysis will be complete; hence no particular missing data handling is necessary.
*Retrospective study based on health insurance claims data from Associations of Statutory Health Insurance Physicians (ASHIPs).*

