*Hypothesis*. If the vaccination uptake increases considerably, related disease incidences will subsequently decrease.*Study population*. See above under primary outcome, vaccination rate.*Outcome measures*. Disease incidences for influenza and pneumococcal diseases among individuals aged ≥60 and in a to be determined subgroup of individuals before vs. after the intervention (2017 - 2019) will be compared in Thuringia vs. outside Thuringia as a function of vaccination uptake.*Statistical analyses*. The health insurance claims data include ICD-10 codes assigned by the physicians specifically for influenza and pneumococcal diseases and disease-related unspecific clinical syndromes. A number of ICD-10 codes that represent the clinical syndromes acute-respiratory infection and influenza-like illness will be selected. For pneumococcal diseases, ICD-10 codes for community-acquired pneumonia and invasive pneumococcal disease will be selected. The data for analysis will be complete; hence no particular missing data handling is necessary.The ICD-10 codes will undergo a data cleaning procedure so that they represent the specific endpoints most accurately. The disease incidence will be calculated as the proportion of diseased patients per year (pneumococcal disease) or per season (influenza disease, third and fourth quarter of calendar year plus first quarter of the subsequent year). The denominator will be taken from the statistics of statutory health insurances [65]. All routine data collected by health insurances and ASHIPs are anonymous.

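### The claims cohort pools both vaccines into one 2014 exposure, so it cannot give vaccine-specific effects on influenza or IPD over 2015–2017

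*Protocol article*

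**What the plan says.** The relevant text is in the Protocol article, Secondary outcomes, study d (the cohort study on AOK PLUS claims data).

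- **Aim and hypothesis.** The study is meant to quantify the impact of influenza and pneumococcal vaccination on influenza, pneumonia, IPD and sepsis. The hypothesis is a single contrast: "The incidences of influenza, pneumonia, IPD and sepsis are lower in people vaccinated than non-vaccinated over 60 years of age".
- **Source population.** "including about 300,000 persons ≥60 years, living in Thuringia".
- **Exposed.** "The exposed cohort group is expected to consist of about 130,000 patients with pneumococcal and/or influenza vaccination in 2014".
- **Unexposed.** "the unexposed cohort group are patients without pneumococcal vaccination in 2008–2017 and without influenza vaccination in 2012–2017".
- **Follow-up.** "The observation period covers the years from 2015 to 2017".
- **Comparison.** Incidence, hospital and ICU admission, and mortality "will be compared between vaccinated and unvaccinated persons".
- **Method.** Multiple regression and propensity score matching.

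The Study population section of the tertiary outcomes reuses the same two groups for costs, with follow-up at 1, 2 and 3 years.

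Elsewhere the protocol keeps the vaccines apart. For the primary coverage outcome, "coverage will be calculated as the proportion of patients vaccinated per year (pneumococcus vaccination) or per season (influenza vaccination" is the rule, and at-risk groups have a five-year look-back for pneumococcal vaccination. Study e counts influenza disease "per season (influenza disease, third and fourth quarter of calendar year plus first quarter of the subsequent year".

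**The concern.** The aim names two vaccines and four diseases, but the exposure is one yes/no variable fixed in calendar year 2014. Two mismatches follow.

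1. **Vaccine against outcome.** Nothing pairs a vaccine with the disease it targets. The IPD comparison includes exposed people with no pneumococcal dose, and the influenza comparison includes exposed people with no influenza dose.
2. **Calendar year against season.** A vaccination that the protocol counts by season is fixed by a 2014 dose and then carried through three further calendar years. Influenza doses in 2015–2017 are used to keep people out of the unexposed group, but have no role in the exposed group.

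Regression and matching address differences between the people in the two groups. They do not change what being exposed means. If the study reports a weak effect on influenza or IPD, the reader cannot tell a weak vaccine effect from diluted exposure. If it reports a strong one, the reader cannot say which vaccine it belongs to. The Discussion acknowledges confounding by indication and healthy vaccinee bias for these cohorts, but not exposure misclassification.

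**Working it through.** **The plan's own figure.** The exposed group is 130,000 of 300,000, or 43.3%. The protocol gives no uptake rates behind it, no split by vaccine and no power calculation for this cohort, so there is nothing further to reproduce.

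**Influenza: season quarters in follow-up.** The season is Q3, Q4 and the next Q1. This definition is stated for study e and borrowed here.

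| Season | Quarters falling in 2015–2017 |
|---|---|
| 2014/15 | 1 (Q1 2015) |
| 2015/16 | 3 |
| 2016/17 | 3 |
| 2017/18 | 2 (Q3 and Q4 2017) |
| Total | 9 |

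A dose in autumn 2014 belongs to 2014/15 and reaches 1 of 9 season quarters (11.1%). Against all calendar time this is 3 of 36 months (8.3%). The two fractions have different denominators. A dose in Q1 2014 belongs to 2013/14, which ends before follow-up starts: 0 of 9.

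**Influenza: allowing for revaccination.** Let f be the share of the exposed group with an autumn-2014 influenza dose, and r the share of those revaccinated in each later season. Both are assumptions, as is no later influenza dose in the rest of the group.

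Covered share of season quarters = f × (1 + 8r) / 9

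| r | f = 1 | f = 0.8 |
|---|---|---|
| 0 | 1/9 = 11% | 9% |
| 0.2 | 2.6/9 = 29% | 23% |
| 0.4 | 4.2/9 = 47% | 37% |
| 0.8 | 7.4/9 = 82% | 66% |

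Coverage is below one half when r < (4.5/f − 1)/8, that is r < 0.44 for f = 1 and r < 0.58 for f = 0.8. These are shares of time. Cases need not be spread evenly over season quarters, and the protocol gives no quarterly incidence.

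**IPD: dilution by influenza-only vaccinees.** Let s be the pneumococcal-vaccinated share of the exposed group (assumed). Ignore doses before 2014, deaths and exits. Total exposed time is 130,000 × 3 = 390,000 person-years. Suppose a true effectiveness of 50% (assumed) and no effect of influenza vaccine on IPD.

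Apparent effectiveness = s × 50%

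| s | Person-years without a 2014 pneumococcal dose | Apparent effectiveness |
|---|---|---|
| 20% | 390,000 × 0.8 = 312,000 | 10% |
| 40% | 390,000 × 0.6 = 234,000 | 20% |
| 60% | 390,000 × 0.4 = 156,000 | 30% |

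The entry rule sets no lower limit on s. Pneumococcal doses before 2014 are not barred in the exposed group and would raise the covered share.

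**The case against.** The strongest reply is that the criticised sentence stands under Study population. It may be only an entry rule spanning three identifiable groups (influenza only, pneumococcal only, both), with stratification and time-varying exposure left to a fuller plan. Vaccination history is clearly ascertained separately for each vaccine. This stands in part: the article does not forbid such analyses. But the hypothesis and the comparison are themselves stated as vaccinated against unvaccinated for all outcomes, and the group is repeated for costs. The point concerns that stated contrast, not missing detail.

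Four further replies limit the point.

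- **Revaccination.** A reader might infer that most exposed time is not exposed to the relevant vaccine. The documents do not support this. They give neither the vaccine mix nor revaccination rates, and with high revaccination most influenza-season time would be covered.
- **Pneumococcal vaccinees.** The five-year look-back used elsewhere suggests that 2015–2017 is relevant exposure time for people who had that vaccine.
- **Shared outcomes.** Pneumonia, sepsis, mortality and total cost can be affected by either vaccine, so a pooled contrast has a meaning there. The mismatch is sharp only for influenza and IPD.
- **Comparator.** It is not a never-vaccinated group. The rule requires no pneumococcal dose in 2008–2017 and no influenza dose in 2012–2017.

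**Conclusion.** The point holds in a limited form. As written, the contrast cannot give vaccine-specific effects on influenza and IPD, although the stated aim calls for the impact of both vaccines on these diseases. The misclassification is likely to dilute both effects, by an amount the documents do not allow one to fix. The 2014 influenza dose alone guarantees at most 1 of 9 season quarters. Actual coverage could run from about 11% to 82% or more, depending on assumed revaccination. For pneumonia, sepsis, mortality and cost, the result is a mixed effect of any vaccine in 2014.

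Dilution is only one force on the estimate. Healthy vaccinee bias, which the Discussion admits, can push towards apparent benefit, so the net direction is not known.

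A reader might also infer that the evaluation of the campaign is undermined. It is not. This cohort compares people by vaccination in 2014, before the 2017 start of the intervention, and the primary outcomes do not use it. The point deserves correction because study d and the whole tertiary outcome rest on this definition.

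**What to change.** Keep the pooled contrast, if wanted, but label it as an any-vaccine analysis. Add vaccine-specific exposure from the same AOK PLUS data, for both study d and the tertiary analysis:

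- **Pneumococcal.** Vaccinated in 2014 versus not, for IPD, pneumonia, sepsis and cost over 1 to 3 years, adjusted for influenza vaccination.
- **Influenza.** Time-varying exposure, updated each season, for influenza, pneumonia, sepsis and cost in that season. Exposed time starts at the vaccination date and time before the dose counts as unexposed. Classifying a whole season by whether a dose was given at some point in it would credit pre-dose time to the vaccinated and create immortal-time bias.
- **Both vaccines.** Report these people separately.
- **Comparators.** Define them to match each analysis, without requiring that people stay unvaccinated through 2017. That requirement selects on the future: someone who dies early cannot be vaccinated later and so stays in the unexposed group, while a survivor may be removed from it.

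The protocol says data from 2008 onward were being acquired and that preparation had just begun, so this needs redefinition and programming rather than new collection. One assumption must be checked: that the insurer's data carry vaccination dates, which the article lists for the ASHIP data but not for AOK PLUS. The price is exposed groups smaller than 130,000, lower precision and more programming. The change should be fixed before results are seen.

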Due to the multi-methods and multi-data sources approach for intervention evaluation the results will be multifaceted, too. While this creates unique opportunities, it also comes with considerable challenges: data may sometimes be difficult to compare. Furthermore, limitations of the individual data sources are the following:Microbiological diagnostics of the secondary outcome pneumonia is not standardised between German hospitals.Although ALERTSNet aims to cover all of Thuringia, it only covers specific centres at certain times.ICD codes used by the German DRG statistics are considered to have high specificity, but only moderate sensitivity, thus being prone to an underestimation of disease prevalence, e.g., for sepsis by up to 3.5-fold [71, 72].Results from cohort studies assessing the impact of vaccination on disease incidences or resource utilisation might be subject to confounding by indication or healthy vaccinee bias. However, relevant covariates will be collected and adjusted analyses will be performed to mitigate this risk.Awareness for the intervention could be so low that stratifying data per material or source of information might be difficult. If awareness is below 50% in the first 100 participants of the representative study after wave one, participants with awareness for the intervention will be oversampled to reach a sample of at least *n* = 350 participants per group. Otherwise, reliable statistical analyses about the effects of the single aspects of the intervention will be not possible.

The intervention is limited to two seasons and an observation period before and after each launch. Some effects of the intervention may only become apparent after a longer period of time and will thus be missed due to the limited duration of the observation.

In sum, this study will add further knowledge to theory-based and evidence-informed development of interventions based on the assessment of relevant behavioural determinants within the target group. Lessons learned from this project can have an additional positive impact on campaign development especially for the growing 60+ age group for various other health behaviours (e.g., healthy diets, physical activity, age-related prevention campaigns such as screenings). The study uses a sophisticated and multi-faceted approach to evaluation, which can identify chances and pitfalls of several data sources. It could therefore serve as a benchmark for future evaluation studies.

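### In the AOK PLUS cohort the look-back for earlier vaccination binds the unexposed only, so exposed persons with earlier vaccination have no unexposed counterpart

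*Protocol article*

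**What the plan says.** The cohort is described in the protocol article under Secondary outcomes, item d (retrospective cohort study on health insurance claims data). The Study population text under Tertiary outcomes repeats the same definitions for the economic analysis.

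- Source: a database study "including about 300,000 persons ≥60 years, living in Thuringia" and insured with AOK PLUS.
- Exposed: "The exposed cohort group is expected to consist of about 130,000 patients with pneumococcal and/or influenza vaccination in 2014". No condition on earlier years is stated.
- Unexposed: "the unexposed cohort group are patients without pneumococcal vaccination in 2008–2017 and without influenza vaccination in 2012–2017".
- Follow-up: "The observation period covers the years from 2015 to 2017".
- Data: "we have commenced in 2017 to acquire the data from 2008 to 2016", so earlier vaccinations should be visible for both groups.
- Analysis: multiple regression and propensity score matching, without a covariate list.

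The Discussion concedes that results of such cohort studies "might be subject to confounding by indication or healthy vaccinee bias" and answers that "relevant covariates will be collected and adjusted analyses will be performed to mitigate this risk".

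**The concern.** The hypothesis sets vaccinated against non-vaccinated people, but the two groups are admitted under different rules. A person vaccinated every year and a person vaccinated for the first time in 2014 are both exposed. A person given pneumococcal vaccine in 2010 and nothing since is in neither group. A person given pneumococcal vaccine in 2010 and influenza vaccine in 2014 is exposed, and any lasting protection from 2010 is then credited to 2014.

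The article itself lists previous vaccinations among the determinants of vaccination behaviour (Further determinants of vaccination behaviour, in the telephone survey). Vaccination history plausibly marks health behaviour and contact with care, and so bears on the two biases that the Discussion names. The entry rule makes that history differ between the groups by construction.

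What is at stake is the reading of the clinical comparisons in item d (incidence, hospital and ICU admission, mortality) and of all cost and utilisation comparisons in the tertiary outcome. The primary outcomes do not use this cohort.

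**Working it through.** The article gives no power, alpha or effect size for this cohort, so there is no planned figure to reproduce. The check is logical first and illustrative second.

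**1. The two entry rules side by side**

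| Period | Exposed | Unexposed |
|---|---|---|
| Pneumococcal, 2008–2013 (6 years) | no condition | none allowed |
| Influenza, 2012–2013 (2 years) | no condition | none allowed |
| 2014 | pneumococcal and/or influenza | neither |

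The exposed share is 130,000 / 300,000 = 43.3%, so at most 300,000 − 130,000 = 170,000 people can be unexposed. Persons vaccinated within the look-back but not in 2014 fall out of both groups.

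**2. Overlap**

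Let *s* be the share of the exposed with a vaccination in the look-back years; the article does not give it. The corresponding share in the unexposed is 0 by definition. Within the cohort, the probability of being exposed given earlier vaccination is therefore 1. No propensity score method can find an unexposed match with that history.

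The standardised difference in earlier vaccination is s / √(s(1 − s)/2). The exposed who do have counterparts number 130,000 × (1 − s).

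| s (assumed) | Standardised difference | Exposed with counterparts |
|---|---|---|
| 0.3 | 0.93 | 91,000 |
| 0.5 | 1.41 | 65,000 |
| 0.7 | 2.16 | 39,000 |
| 0.9 | 4.24 | 13,000 |

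**3. Possible size of the bias, illustration only**

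Assume that vaccination has no effect, that earlier vaccinees have RR times the risk of others for unrelated reasons, and that other covariates remove none of this. Then

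spurious effectiveness = 1 − [(1 − s) + s × RR] = s × (1 − RR).

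| RR (assumed) | s = 0.5 | s = 0.7 | s = 0.9 |
|---|---|---|---|
| 0.9 | 5% | 7% | 9% |
| 0.8 | 10% | 14% | 18% |
| 0.7 | 15% | 21% | 27% |

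If earlier vaccinees are frailer (RR above 1), the sign reverses and vaccination looks harmful.

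**4. What regression does**

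Poisson data were simulated for 130,000 exposed and 170,000 unexposed, with a base rate of 0.05, RR = 0.8 and no true effect of 2014 vaccination. The rate ratios for exposure were:

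| s | Earlier vaccination not in model | Earlier vaccination in model |
|---|---|---|
| 0.5 | 0.89 (95% CI 0.86–0.92) | 1.00 (0.96–1.04) |
| 0.9 | 0.81 (0.79–0.84) | 1.06 (0.98–1.15) |

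The second column is compatible with the true value of 1. However, the exposure estimate then comes only from exposed persons without earlier vaccination. Carrying it over to the rest assumes the same effect in them, which these data cannot test.

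**The case against.** A reader might infer that no planned adjustment can deal with earlier vaccination at all. The documents do not support that. Regression is planned, data from 2008 are being acquired, and the simulation shows that a model containing earlier vaccination recovers a null effect. Exact matching on history would also give a valid contrast. Both apply to 2014 vaccinees without earlier vaccination. The article does not say that the analysis will be restricted in this way or that history will be a covariate, although the covariate list may stand in a fuller document. What remains is the narrower statement about the full exposed group.

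Earlier vaccination is a marker, and what must be balanced is the underlying risk. Age, comorbidity and earlier use of care may capture part of it. This stands, and it is why the percentages above are not estimates of bias.

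A comparator free of recent vaccination keeps residual protection out of the unexposed. That is a reasonable purpose, but it does not explain why the exposed carry no matching condition, and earlier doses in the exposed can bring the same residual protection into their side.

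A contrast of new vaccinees changes the question and may carry its own confounding by indication, since a first vaccination can follow a change in health. This also stands. It argues for showing both analyses rather than replacing one by the other.

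Finally, the Discussion already discloses the bias and claims only to mitigate it. True, but it relies on adjustment and does not mention that the entry rule limits what adjustment can do.

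**Conclusion.** The one-sided look-back is explicit, is stated twice, and nothing else in the article repairs it. In the full exposed group, earlier vaccination cannot be balanced by matching and can be handled by regression only through extrapolation. The comparison as defined is of 2014 vaccinees of any history with long-term non-vaccinees.

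The size and direction of the resulting bias are unknown. The 10% to 18% figure rests on an assumed risk ratio of 0.8, an assumed 50% to 90% with earlier vaccination, no vaccine effect and no benefit from other covariates. It shows only that the bias could be large enough to matter.

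It would go too far to conclude that the cohort can say nothing about vaccination: a valid contrast exists within the same data for 2014 vaccinees without earlier vaccination. The finding affects one of five secondary data sources and the tertiary outcome. It deserves correction but does not threaten the main evaluation of the campaign.

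**What to change.** For secondary outcome d and the tertiary outcome, pre-specify an additional analysis with a symmetric look-back:

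- Exposed: vaccinated in 2014, with no pneumococcal vaccination in 2008–2013 and no influenza vaccination in 2012–2013.
- Unexposed: as now defined, since they already meet this look-back.
- Both groups: the same required insured time over the look-back years, so that absence of a claim means the same thing in each.

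Report this beside the planned contrast. Describe the planned contrast as 2014 vaccinees of any history versus long-term non-vaccinees, and attribute differences to vaccination only where the two analyses agree.

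The requirement that the unexposed also stay unvaccinated through 2015–2017 is a separate issue, which this change leaves as it is.

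Cost: recoding of cohort entry. The claims years needed are already being acquired, and the article says data preparation has only just begun. The price is precision: if 10% to 30% of the 130,000 are new vaccinees (assumed), 130,000 × 0.10 = 13,000 to 130,000 × 0.30 = 39,000 exposed persons remain, with wider intervals for rare outcomes such as invasive pneumococcal disease. The result also speaks for new vaccinees only, which the report should say.
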